## **3. STUDY DESIGN**

A randomized controlled design will be carried out, in which the effectiveness and user-friendliness of an online app-based VR self-help treatment 'ZeroPhobia: Aviophobia' and 'ZeroPhobia: Arachnophobia' will be evaluated. In this study, 96 (aviophobia) and 72 (arachnophobia) participants from the Dutch general population will be randomized in 2 separate RCTs over 2 conditions: the experimental condition (ZeroPhobia: Aviophobia or Arachnophobia) and a waitlist control condition. The duration of the intervention will be 6 weeks. Measures will be taken at baseline, directly after the intervention (6 weeks) and at 3- and 12- month follow-ups. All measures will be completed online. Subjects in the wait-list condition will receive the intervention after completion of the post-test. Randomization (block randomization with 6, 8, 10, and 12 blocks) will be performed by an independent researcher. Figure 1 presents the flow chart of the study.

[figure not shown]

Figure 1: flow chart

#### 4. STUDY POPULATION

##### 4.1 Population (base)

A sample of 96 individuals (18 – 64 years) with symptoms of fear of flying (aviophobia) and 72 individuals with symptoms of fear of spiders (arachnophobia) will be recruited from the Dutch population.

#### **4.2 Inclusion criteria**

In order to be eligible to participate in this study, a subject must meet all of the following criteria:

- Aviophobia: scoring above 56 on the Flight Anxiety Situations questionnaire (FAS; van Gerwen et al., 1999; 2018; Nousi et al., 2008)
- Arachnophobia: scoring above 80 on the Fear of Spiders Questionnaire (FSQ; Szymanski et al., 1995)
- between 18 – 64 years old
- have access to a compatible smart phone with internet
- willing to participate in the research study and provide informed consent

#### **Exclusion criteria**

A potential subject who meets any of the following criteria will be excluded from participation in this study:

- have insufficient knowledge of the Dutch language
- are under current treatment for specific phobia or psychotropic medication (unless on stable dosage for the previous 3 months and no changes planned during the study period).

#### **4.3 Sample size calculation**

Aviophobia: An effect size of Cohen's  $d = 0.80$  was found from a meta-analysis of VR treatments for fear of flying (Fodor, 2018). Because ZeroPhobia: Aviophobia is a complete self-help treatment with rudimentary VR glasses, we have taken a slightly more conservative effect size of 0.70 as the starting point for the power calculation. To demonstrate a difference between the experimental and control condition with a standardized effect size of  $d = 0.70$  (tested on both sides), an alpha of 0.05 and a statistical power (1-beta) of 0.80, we have 34 respondents in each condition required (68 respondents in total). Taking into account a drop-out rate of 40% (Donker et al., 2019), we need a total of 96 respondents ( $n = 48$  per condition).

Arachnophobia: An effect size of Cohen's  $d = 1.11 / 1.12$  was found from a meta-analysis of VR treatments for different phobias, including fear of spiders (Opris et al., 2012,

Powers et al., 2008). Because ZeroPhobia: Arachnophobia is a complete self-help treatment with rudimentary VR glasses, we have taken a slightly more conservative effect size of 0.80 as the starting point for the power calculation. To demonstrate a difference between the experimental and control condition with a standardized effect size of  $d = 0.80$  (tested on both sides), an alpha of 0.05 and a statistical power (1-beta) of 0.80, we have 26 respondents in each condition required (52 respondents in total). Taking into account a dropout rate of 40% (Donker et al., 2019), we need a total of 72 respondents ( $n = 36$  per condition).

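### The totals of 96 and 72 do not cover the planned 40% drop-out: they leave 57.6 and 43.2 participants against the 68 and 52 required, so power under equal loss is about 74% and 73%, not 80%

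*Protocol*

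**What the plan says.** Protocol section 4.3 sizes each trial in two steps.

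- **Aviophobia.** The planning effect is a "slightly more conservative effect size of 0.70 as the starting point for the power calculation", reduced from a meta-analytic 0.80. The test is two-sided ("tested on both sides"), with alpha 0.05 and "a statistical power (1-beta) of 0.80". From this, "we have 34 respondents in each condition required (68 respondents in total"). After an allowance for 40% drop-out, "we need a total of 96 respondents", that is 48 per condition.
- **Arachnophobia.** With d = 0.80, reduced from 1.11/1.12, and the same alpha and power, "we have 26 respondents in each condition required (52 respondents in total"). After the same 40% allowance, "we need a total of 72 respondents", that is 36 per condition.

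The Summary and sections 3 and 4.1 repeat 96 and 72. Section 4.3 does not write out the inflation formula, and it uses no baseline/post-test correlation or other gain in precision. Section 8.2 sets 1:1 allocation. Section 10.1 plans repeated measures ANOVA for the intention-to-treat analysis, t-tests for the per-protocol analysis, and multiple imputation under missing at random.

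**The concern.** The allowance exists so that the required number is still there after the expected loss. Here it is not: 60% of each total is less than the number the same section calls required. Both trials have the gap, so a single misprint is an unlikely explanation.

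At stake is the one power figure that justifies both sample sizes. On the plan's own inputs, the chance of missing a true effect of the planned size is about 26% and 27%, not 20%.

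**Working it through.** **Inputs, all from section 4.3 except the last:** two-sided alpha 0.05; power 0.80; d = 0.70 and 0.80; required 34 and 26 per arm; drop-out 40%; totals 96 and 72; 1:1 allocation (section 8.2).

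**1. Reproduce the base sizes.** A two-sample t-test (noncentral t) needs n = 33.02 per arm at d = 0.70, rounded up to 34, and n = 25.52 at d = 0.80, rounded up to 26. Power at 34 and 26 per arm is 0.812 and 0.807. The base sizes are correct.

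**2. Reproduce the totals.** Two inflation rules were tried:

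| | Required | × (1 + 0.4) | ÷ (1 − 0.4) | Stated |
|---|---|---|---|---|
| Aviophobia | 68 | 95.2 | 113.3 | 96 |
| Arachnophobia | 52 | 72.8 | 86.7 | 72 |

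Multiplication gives 96 after rounding up, and 72 only after rounding down (26 × 1.4 = 36.4 per arm, stated as 36). Division does not give either total. With equal arms it gives 114 (57 per arm) and 88 (44 per arm), which is 18 and 16 more than planned.

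**3. Apply the planned loss to the stated totals.**
- Aviophobia: 96 × 0.6 = 57.6, or 28.8 per arm, against 34 required.
- Arachnophobia: 72 × 0.6 = 43.2, or 21.6 per arm, against 26 required.

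**4. Power at those numbers** (completers, two-sided t-test, alpha 0.05, equal loss in both arms):
- d = 0.70 with 28.8 per arm: 0.742 (0.730 at 28, 0.745 at 29).
- d = 0.80 with 21.6 per arm: 0.728 (0.716 at 21, 0.736 at 22).

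The effects detectable with 80% power become d = 0.75 and d = 0.87.

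**5. Drop-out that the totals do cover.** 1 − 68/96 = 29.2% (28 participants) and 1 − 52/72 = 27.8% (20 participants).

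**6. Sensitivity to where the loss falls.** With 40% lost in the intervention arm only (28.8 against 48, and 21.6 against 36), power is 0.834 and 0.823.

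**7. Sensitivity to use of the baseline score.** The documents give no baseline/post-test correlation ρ, so a range is assumed, still with 40% lost in both arms. For ANCOVA of the post-test score the effective effect is d/√(1 − ρ²). For a group-by-time (change) test it is d/√(2(1 − ρ)).

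| ρ | ANCOVA, aviophobia / arachnophobia | Change test, aviophobia / arachnophobia |
|---|---|---|
| 0.3 | 78% / 77% | 60% / 58% |
| 0.4 | 81% / 80% | 66% / 65% |
| 0.5 | 85% / 84% | 74% / 73% |
| 0.6 | 90% / 89% | 83% / 82% |

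ANCOVA reaches 80% from a correlation of about 0.37 (aviophobia) and 0.41 (arachnophobia).

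**The case against.** The arithmetic gap itself has no answer in the document, but its consequence can be contested.

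- **Drop-out may not mean a missing outcome in both arms.** Section 4.3 does not say whether drop-out is from the app or from the post-test. Section 1 links drop-out to guided or unguided use, section 8.6 promises follow-up after withdrawal from treatment, and waitlist participants have no treatment to leave before the post-test (section 8.3). If only the intervention arm lost 40%, power would exceed 80%. This stands as a reason to state the assumption. It does not rescue the totals, because section 4.3 inflates both conditions equally.
- **The planning effects are discounted.** At the cited 0.80 and 1.11, power with the same loss is 0.85 and 0.95, and section 6.3 reports d = 1.14 in the programme's earlier app trial. This limits the practical harm, but the protocol claims 80% at the discounted effects.
- **Multiple imputation keeps everyone in the analysis.** It keeps them in the data set, but it does not by itself replace the lost post-test information. By inflating for drop-out, the plan itself treats the loss as costing information.
- **The repeated measures analysis may gain precision.** It may, but section 4.3 claims no such gain. The change test gains nothing at a correlation of 0.5 and loses power below it.
- **A misleading null result.** Section 10.1 plans effect sizes with confidence intervals, which would show the precision achieved. The error therefore misstates the design more than it would distort the reading of the results.

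A reader might also take multiplication by 1.4 as established. The protocol never writes it, and the arachnophobia total fits only by rounding down. It is the likely explanation, not a stated one.

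**Conclusion.** The error is real and affects both trials. The required 34 and 26 per arm are right; the totals of 96 and 72 do not deliver them at the planned 40% drop-out. Power is about 74% and 73%, a shortfall of 6 to 7 points. That size rests on equal 40% outcome loss in both arms and a completer t-test at two-sided alpha 0.05.

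Two stronger readings are tempting, and the documents support neither. One is that both trials fall short of 80% power whatever happens: that does not follow if the loss is confined to the intervention arm or if larger effects hold. The other is that baseline adjustment would certainly restore the power: that depends on a correlation the protocol does not give, and at 0.3 it would not. The shortfall is moderate and does not invalidate the design, but the stated 80% is wrong as written.

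**What to change.** Keep 96 and 72 and correct section 4.3. State that at 40% outcome loss in both arms power is about 74% (aviophobia, d = 0.70) and 73% (arachnophobia, d = 0.80). Equivalently, state that the required 34 and 26 per arm are reached only if drop-out is at most about 29% and 28%. Say there that drop-out means a missing post-test and that it is assumed equal in both arms. The cost is wording in one section and a less favourable power figure, with no extra enrolment.

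If the sponsor prefers to keep the 80% claim at 40% drop-out, the totals become 114 and 88 (34.2 and 26.4 expected completers per arm, power about 81% in each trial). That costs 18 and 16 more participants and changes the Summary and sections 3 and 4.1.

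Optional and separate: a baseline-adjusted ANCOVA of the post-test score as the primary analysis. Section 10.1 would have to be amended as well, since it specifies repeated measures ANOVA, although it also leaves the procedure open to review before analysis. Any recovered power should be given over a range of correlations, as in the table above, not at one assumed value.

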## 5. TREATMENT OF SUBJECTS

### 5.1 Investigational product/treatment

ZeroPhobia is based on the principles of virtual reality exposure therapy (VRET) and Cognitive Behavioral Therapy (CBT). These therapies are currently the most researched and used treatments for anxiety disorders. ZeroPhobia is developed by Vrije Universiteit Amsterdam and In-Session. The content is developed by both, whereas In-Session alone is responsible for app-programming and VR development. ZeroPhobia has been tested by persons with aviophobia symptoms throughout the process of development. In a recent ZeroPhobia user-test, the VR environment was tested in 10 healthy participants. Results showed that the VR environment was rated as realistic and that subjects felt they were present in the environment. Among those who had symptoms of aviophobia, the level of anxiety raised with increased levels of difficulty of the VR environment. Anxiety reduced afterwards. ZeroPhobia: Arachnophobia will be tested among healthy participants soon.

Both ZeroPhobia: Aviophobia as well as ZeroPhobia: Arachnophobia are app-based interventions consisting of six modules that can be followed according to a user's own tempo and timing and without the intervention of a therapist. ZeroPhobia: Aviophobia is entirely unguided, whereas ZeroPhobia: Arachnophobia is guided. The participant will download the app on his or her smartphone. The program can be viewed from their mobile phone. Only when practicing in the VR environment (1 module) participants will put their mobile phone into the provided cardboard VR glasses to be able to experience the VR environment. Participants are allowed to keep the VR glasses after finishing the study.

The therapy consists of six consecutive modules, each taking between 5 to 20 minutes to complete:

1. Psychoeducation: Explanation of a specific phobia and ZeroPhobia
2. Facing your Fears: Setting your goals, explanation about exposure and the fear curve.

3. Exposure Therapy: Practicing in virtual reality and exposure feedback
4. Cognitive Therapy: Detecting automatic thoughts
5. Cognitive Therapy: Developing helping thoughts
6. The Next Steps.....: Facing your fears in daily life

Ad 1) **Psychoeducation**: Explanation of what a specific phobia exactly entails, how it can emerge and what the potential consequences are.

Ad 2) **Facing your fears**: In this module, the participant will define his/her goals for the treatment. Furthermore, the treatment principles underlying exposure are explained.

Ad 3) **Exposure in VR**: in this module, the VR content is explained and how to access it. Participants will practice in a practice-environment with VR before commencing the exposure therapy. After practice, the actual exposure takes place. In the VR environment, participants are exposed to situations involving flying/spiders. Participants can set the level of fear they would like to induce in the environment. Participants are informed that they can remove their VR glasses and exit the exposure at any time, especially if the fear induced is too challenging for them. After completing an exposure and based on his/her fear levels and performance, the user receives feedback. S/he can return to practicing in virtual reality as often as s/he likes and gradually expose him-/herself to different flight or spider situations and fear intensities. Only during the exposure sessions will the participant use the VR glasses.

Ad 4 and 5) **Cognitive therapy**: In these modules, according to the well-established principles of CBT, users identify and evaluate their catastrophic thoughts regarding their fear (e.g., “the airplane will crash” or “the spider will hurt me”).

Ad 6) **The Next Steps**: This module contains information on how the user can continue his/her practice and further reduce his/her fear and prevent relapse. This includes developing an individualized fear hierarchy. A fear hierarchy contains the necessary steps that need to be taken to reach one’s goals in the therapy. Explicit attention is devoted to motivation and encouragement.

The program further consists of:

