## SUMMARY

**Rationale:** Specific phobias, such as intense fear of flying, heights, or spiders, are the most common forms of mental health disorders worldwide. Specific phobias have a lengthy history of clinical research and very effective treatment for specific phobias using exposure therapy already exist (Wolitzky-Taylor et al., 2008). However, due to high costs, stigma, and long waiting lists, access to evidence-based therapy is currently limited. Meta-analyses on treatment effectiveness for people suffering from specific phobias have shown that Virtual Reality Exposure Therapy (VRET) is as effective as traditional forms of exposure therapy (Marino et al., 2015; Parsons and Rizzo 2008; Powers and Emmelkamp 2008; Opris et al., 2012). VRET, however, involves relatively high costs and limited accessibility, which make it prohibitive for the larger part of the population. This project capitalizes on novel technology and recent scientific advances to develop an affordable treatment modality that is available for anybody, anywhere. Specifically, we will develop and test ZeroPhobia, a self-help VRET for aviophobia and arachnophobia, delivered through a smartphone application (app) in combination with rudimentary cardboard Virtual Reality (VR) glasses. We hypothesize that ZeroPhobia is effective in reducing anxiety symptoms and is user-friendly.

**Objective:** To determine (1) the clinical effects of ZeroPhobia to reduce aviophobia and arachnophobia symptoms at post-test, (2) the clinical effects of ZeroPhobia at 3- and 12-month follow-ups, (3) the user-friendliness of the intervention, (4) if the usage intensity and/or (5) the feeling of presence influence the primary outcome of ZeroPhobia, (6) if exposure or evaluating thoughts mediate anxiety outcomes, (7) if guided VRET results in reduced participant dropout rates, and (8) whether or not ability to fantasize influences the effectiveness of VRET.

**Study design:** This project involves two randomized controlled trial (aviophobia and arachnophobia) with two arms: the intervention condition (ZeroPhobia) and a waitlist control condition.

**Study population:** For aviophobia  $n = 96$  and for arachnophobia  $n = 72$  individuals (18-65 years) who experience aviophobia or arachnophobia symptoms, respectively, will be recruited from the general population to participate in the trial.

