Research into mobile apps as a method to intervene for psychiatric disorders are promising (e.g. Donker et al., 2013; Eysenbach et al., 2011; Saeb et al., 2015). App-based mental health interventions based on e.g. CBT principles have shown to be effective in reducing mental health symptoms with within-group and between-group intention-to-treat effect sizes ranging from  $d = 0.29 - 2.28$  and  $0.01 - 0.48$  at post-test and follow-up, respectively in a review of Donker et al. (2013). Advantages are better accessibility and participant retention, real-time progress monitoring, portability, and flexibility. As far as we know, one study has investigated the effectiveness of VRET using a mobile application for fear of spiders. Results showed a reduction in anxiety levels (Piercey et al., 2012). Another study investigating VRET on a smartphone has recently found VRET to be effective at reducing spider phobia symptoms and non-inferior to traditional one-session exposure therapy (Miloff et al., 2019).

Recently, we have explored the feasibility and efficacy of ZeroPhobia: Acrophobia, a VRET delivered through a smart phone app using Google cardboards for fear of heights (Donker et al., 2019). The randomized controlled trial (RCT) demonstrated large effect sizes and ZeroPhobia: Acrophobia was rated user-friendly. The aim of the proposed project is to test a (similar) low cost, scalable, and evidence-based solution for aviophobia and arachnophobia symptoms through exposure therapy by integrating VR technology with a smart phone app in two separate RCTs. Both interventions will be tested for its effectiveness in reducing anxiety symptoms and user-friendliness. ZeroPhobia: Arachnophobia will differ

from ZeroPhobia: Aviophobia in that it will be a guided VRET, in order to determine whether drop-out rates are lower than previous, unguided trials of ZeroPhobia. The study will be of a randomized controlled trial (RCT) design and will be conducted amongst adults from the general Dutch populations with aviophobia and arachnophobia symptoms.

We hypothesize that both ZeroPhobia applications will effectively reduce anxiety symptoms as well as be rated as user friendly.

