## **2. OBJECTIVES**

Primary Objective: To determine the clinical effects (a reduction in anxiety symptoms – aviophobia and arachnophobia at post-test [between the experimental condition and controls]) of ZeroPhobia, and whether effects are sustainable at 3- and 12-month follow-up (a reduction in anxiety symptoms between baseline and follow-up for those in the experimental condition)

Secondary Objective(s): To determine the user-friendliness of ZeroPhobia, if it is effective in reducing depression and anxiety, to determine whether usage intensity and presence in the VR environment influences the effects of ZeroPhobia, to determine whether exposure or evaluating thoughts mediate anxiety outcomes, to determine whether or not guided VRET is related to reduced participant drop-out rates, and whether ability to fantasize influences the effectiveness of VRET.

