This survey will allow them to provide a physical mailing address, so hard copies of consent and informational materials can be mailed to them. Screening questions will also include items about age, Dutch fluency, whether or not they are currently receiving psychiatric services for their phobia, and either the FAS or FSQ (duration of 15 minutes). This screener is given prior to official consent in order to save ineligible participants time and prevent unnecessary baseline data from being collected. If participants do not meet inclusion criteria, an automatic email will be sent to them notifying them of their exclusion and the reasoning of such. If participants are

eligible, a trigger email will be sent to the researchers to let us know they meet criteria to participate. This screening information will not be used for any other purposes other than to determine inclusion and exclusion; all screening survey responses will be deleted after participant's eligibility has been determined.

If eligible, according to the basic screener, and still interested, the research assistant will send the patient information letter and informed consent form to their home address with a return envelope. If necessary, the researcher will remind them by email to complete the informed consent (2 reminders in total, second being a phone call). The informed consent form will be sent to each participant. The participant will be instructed to sign the consent form and mail it back to us. Once received, we will sign the consent form as well and then make a copy of the consent form. This copy will be mailed back to the participant to keep for their own records.

Upon receiving informed consent, the researcher will send a second survey link to participants via email to complete a baseline measurement. In this baseline measurement, demographic variables (gender, level of education, marital level), FAM (aviophobia) or SPQ (arachnophobia), PHQ, BAI, WSQ, and IRI will be measured (duration of 20 minutes).

If necessary, the researcher will remind them by email to complete the baseline measurement (2 reminders in total, second being a phone call). After the baseline has been completed, participants will be randomized by an independent researcher. The research assistant will notify the participant of which condition they have been randomized to, either the intervention condition or the waitlist condition.

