If in the intervention condition, the research assistant will send the VR glasses to the participant by postal delivery, along with usage instructions. The research assistant will email the participant with instructions on how to download the ZeroPhobia app to his/her smartphone. The app is locked with an individual code which will be given to the participant at the start of the intervention. Participants can then begin the ZeroPhobia intervention which they can follow for 6 weeks (5-20 minutes per week, in addition to VRET from module/week 3 onward, which we recommend 10 minutes a day of practice with). When practicing in VRET, participants are asked to fill in one question about their anxiety level before, during, and after VRET (duration: 5 seconds). Participants can follow the intervention at their own pace. Participants will receive weekly automatic reminder emails to begin or continue the intervention from the research assistant. If needed (e.g., with a question about how to use ZeroPhobia or in the unlikely case of distress), participants will be invited to contact the research assistant.

If in the wait-list condition, the participant will be informed that after a six week pause and the completion of a post-test assessment, they can begin the ZeroPhobia program. The wait-list group will undergo the same program procedure as those in the treatment condition. Participants of both conditions will begin the program on the first working Monday after

completing the baseline and being randomized to a condition, meaning participants of both groups will have different start and end times. Both groups will have the same duration of each section, however (see flowchart).

The aforementioned post-test (occurring after 6 weeks of either intervention or pause, or after the completion of module six in the intervention group (for those participants who choose to work through the ZeroPhobia program faster) consists of the FAS and FAM (aviophobia) or FSQ and SPQ, (arachnophobia), PHQ, BAI, IPQ, SUS, CEQ and NEQ, questions regarding whether they received professional treatment during this time, and questions about flight usage (duration: 25 minutes). Two reminders will be given across two weeks to fill in post-test, the first being an e-mail and the second a phone call.

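### The arachnophobia app is called guided but no guidance is described, and the drop-out objective built on it cannot show a causal effect

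*Protocol*

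**What the plan says.** Section 5.1 distinguishes the two apps by guidance: "ZeroPhobia: Aviophobia is entirely unguided, whereas ZeroPhobia: Arachnophobia is guided". The sentence before it covers both apps and says they are followed at the user's own "tempo and timing and without the intervention of a therapist".

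Section 1 gives the reason for guiding the arachnophobia app: "in order to determine whether drop-out rates are lower than previous, unguided trials of ZeroPhobia". Two places turn this into an objective. The summary lists it as "7) if guided VRET results in reduced participant dropout rates", and section 2 lists it among the secondary objectives as "to determine whether or not guided VRET is related to reduced participant drop-out rates".

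Section 8.3 describes what participants receive during the six weeks. On support, it says "Participants will receive weekly automatic reminder emails to begin or continue the intervention from the research assistant", and it invites participants to contact the research assistant if they need to, for example with a question about use or in case of distress. Neither sentence names a trial.

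The comparator in each trial is a waitlist (section 3). The earlier ZeroPhobia trial that the protocol describes was self-guided and concerned fear of heights (sections 1, 6.3 and 11.3).

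**The concern.** Guidance is the exposure in a stated objective, so the protocol has to say what it consists of. Who gives it, through what channel and how often is intervention content. It belongs in sections 5.1 and 8.3 and would not normally be left to an analysis plan.

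Without it, staff running the arachnophobia trial have only the general procedure to follow. They would either give no guidance beyond that procedure or improvise. The drop-out figure would then be attached to an exposure that is undefined and unrecorded.

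The second problem is one of inference. The summary's wording is causal, but no randomised contrast in either trial varies guidance. A lower drop-out rate than in an earlier trial could be reported as an effect of guidance when the design cannot separate it from differences in phobia, sample, app content or calendar time.

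**Working it through.** The plan gives no figure on this point, so the check is a comparison of the text.

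**Step 1. What could count as guidance?** Section 5.1 rules out a therapist for both apps. Guidance must therefore be support from someone else, or support built into the app.

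**Step 2. Which support elements are written, and are any specific to arachnophobia?**

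| Element | Where | Limited to arachnophobia? |
|---|---|---|
| Automated weekly e-mail reminders | 8.3 | No |
| Research assistant on request | 8.3 | No |
| Animated instructions and feedback after exposure | 5.1 | No, common to both apps |
| Clinician support after an adverse emotional reaction | 11.3 | No, common to both apps |

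Of the two support elements that 8.3 writes for the intervention period, 0 of 2 are limited to one app. The case characters and VR scenes in 5.1 do differ by app, but they are content, not guidance.

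**Step 3. Can the label be reconciled with the procedure?** If reminders and on-request contact count as guidance, the aviophobia app as written receives them too and is not entirely unguided. If they do not count, nothing written makes the arachnophobia app guided. Under either reading, the text supplies no difference in guidance between the apps.

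**Step 4. Is guidance recorded?** The usage data in 8.1.3, the measures in Table 1 and the app data in 12.1 cover practice, module use, in-app exercises, anxiety ratings and questionnaires. None records guidance contacts, so the amount delivered could not be recovered afterwards.

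**Step 5. What could the comparison show if guidance were specified?**

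- Within the arachnophobia trial, the contrast is app against waitlist. There is no unguided arachnophobia arm.
- The comparator named in section 1 is earlier unguided ZeroPhobia trials. The one that the protocol describes treated fear of heights, so guided against unguided coincides with spiders against heights.
- Using the parallel aviophobia trial as the unguided reference would not help. It is a separate trial in a different phobia.

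The comparison is therefore non-randomised, and against any unguided ZeroPhobia reference that the protocol describes it crosses phobias. The association wording in section 2 can be met descriptively. The causal wording of summary item 7 cannot.

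**Step 6. How far does it reach?** The summary lists 8 objectives, and this affects 1 of them (item 7, repeated in section 2). The arachnophobia sample size rests on d = 0.80 for app against waitlist and on a drop-out allowance taken from the earlier trial. Neither uses an effect of guidance, so n = 72 does not move on this ground.

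**The case against.** The strongest reply is that section 8.3 is silent rather than contradictory. It sets out one general procedure and never says that the two apps get identical support. A reader might infer a statement of equal support from it, but the document does not make one. That stands, and the point is limited accordingly: guidance is labelled and not described, and the procedure as written contains none that is specific to arachnophobia.

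A reader might also argue that the omission is telling because 8.3 separates the trials elsewhere, as in "FAM (aviophobia) or SPQ (arachnophobia), PHQ, BAI, WSQ, and IRI will be measured". That inference is weak. The post-test and follow-up lists in 8.3 and Table 1 include flight usage without restricting it to aviophobia, although 8.1.2 and 10.2 plainly tie flights to that trial. An unmarked item in 8.3 does not prove that both trials receive it.

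A third tempting reading is that section 4.3 contradicts the label, since it says "Because ZeroPhobia: Arachnophobia is a complete self-help treatment with rudimentary VR glasses". It does not. Self-help with light non-therapist guidance is a coherent treatment, and 5.1 places the no-therapist statement and the guided label side by side. Section 4.3 needs no correction on this ground.

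Nor is it open whether the arachnophobia app is meant to be guided, because sections 1 and 5.1 both say so. Only the form of the guidance is missing.

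Finally, section 1 openly declares a comparison with earlier trials, and section 2 asks only about a relation. A descriptive comparison is therefore possible once guidance is defined, and it would go too far to say that the objective could never be addressed. None of this supplies the missing guidance or supports the causal wording in the summary.

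**Conclusion.** The concern holds in this form: the protocol makes guidance the distinguishing feature of the arachnophobia app and the exposure in an objective, yet describes no guidance. Followed as written, the procedure delivers none that separates the two apps. Once guidance is specified, the comparison with earlier unguided trials is still non-randomised and, for the trial described, crosses phobias. It cannot show that guidance reduces drop-out.

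The size is modest: one of eight listed objectives and the description of one intervention. The randomised app-versus-waitlist contrast, d = 0.80 and n = 72 are unaffected.

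The conclusion rests on the protocol text. The flow chart in section 3 is not shown and could contain a guidance step, although 8.3 refers to it only for the duration of each study section. It also assumes that no other operational document, such as a manual, defines the guidance; the protocol cites none for this purpose.

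**What to change.** If guidance will be given, as sections 1 and 5.1 state:

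- Add an arachnophobia-only guidance step to 5.1 and 8.3, naming the provider, the channel and the frequency. Say whether waitlist participants receive it when they start the programme after post-test.
- Have staff log each contact per participant, and list the log among the measures in 8.1.3 and Table 1.
- Reword summary item 7 and section 2 along these lines: to describe drop-out in the guided arachnophobia app and set it beside drop-out in earlier unguided ZeroPhobia trials, as a non-randomised comparison that does not isolate guidance.

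If no guidance will be given, remove the label from sections 1 and 5.1 and the drop-out objective from the summary and section 2. The sponsor should confirm which applies.

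The first option costs a contact log, some wording and whatever staff time the intended guidance already implies. The second costs one secondary objective. Neither changes the sample size, the randomisation or the primary analysis.
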